#### Reported signs and symptoms during palliative sedation

The presence of the following clinical signs and/or symptoms will be registered in the daily monitoring forms: breathing difficulties (dyspnea, rattle); respiratory secretions; (drug induced) delirium; paradoxical reaction/agitation; patients regaining consciousness; and other clinical observations.

#### Evaluation of the palliative sedation trajectories by the attending health care professionals

The attending health care professionals will be asked about their evaluation of the palliative sedation period for the specific patient. Daily rating of the effectiveness of palliative sedation at patient’s comfort level will be scored on a Likert Scale ranging from excellent to very poor.

1 week after the participants death, a questionnaire will be sent to one of the health care professionals, with three questions 1) about their personal rating of agreement to start palliative sedation in this patient, scored on a Likert scale ranging from 1 strongly disagree to 5 strongly agree, 2) the overall effect of the palliative sedation at the comfort levels, and 3) the quality of dying in the particular patient’s case, both scored on a 5-points Likert scale ranging from 1 very poor to 5 excellent.

#### Evaluation of the palliative sedation trajectories by one of the relatives

Two different methods will be used to evaluate the experiences of the relatives with the palliative sedation. First, a daily reporting by the attending health care professionals in the case report forms of expressed concerns and/or complaints of relatives during the palliative sedation period.

Furthermore, at least 1 month after the participant’s death, a structured questionnaire will be sent to one of the relatives. This family satisfaction with care questionnaire (FAMCARE-2) contains 17 items about the care received, which are scored on a Likert scale between 1 very unsatisfied to 5 very satisfied [18].

#### Medication used during the palliative sedation period

Changes in type-, dose- and route of administered sedative(s) and other medication during the palliative sedation period will be recorded daily on monitoring forms from the start of palliative sedation until the time of death.

This medication list contains information about: 1) Changes in dosages of sedative medication which is recorded in numbers and units (mg or mg/hr.); 2) Changes in the sort of sedative medication used for palliative sedation which are recorded with the medication name; 3) Changes in the route of administration of sedative medication. All changes will be recorded with the accompanying date and time.

#### Clinical aspects of decision making

During the decision-making process about palliative sedation, the involved health care professionals will complete questionnaires regarding aspects related to this process. The questionnaires contain questions regarding the initiation and timing of the decision-making and the involvement of various stakeholders (patient, relatives, health care professionals) in different stages of the process.

### Statistical analysis

Statistical analysis will be performed using SPSS, version 25 (SPSS, 2017, Inc. Chicago, IL) and R software, version 3.6.0 (The R Foundation for Statistical Computing, Vienna, Austria).

Missing data will be explored, reason for missing data will be reported and, when missing at random, they will be imputed with multiple regression imputation [19].

We will use a multilevel approach for analysis of changes in the repeated measures of discomfort and levels of sedation during palliative sedation. We will use these measurements as dependent variables and time and baseline measurements as independent variables. Secondary analyses will include possible confounding or effect modifying factors such as age, gender, country and setting.

Descriptive analysis will be performed, using proportions for categorical variables and mean with standard deviations for continuous variables, or median with interquartile range for data with skewed distribution.

Differences between settings will be tested through a Chi-square test for categorical variables (Fischer’s exact test in case of cell frequencies < 5), Kruskal-Wallis test for ordinal variables, and ANOVA for continuous variables.

The association between variables such as age, gender, country, setting, primary diagnosis, performance status and amount of symptom burden, with dosages of medication, levels of discomfort and length of sedation as continuous dependent variables, will be analysed in multivariable analyses.

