### Sample size calculation

In the study by van Deijck and colleagues [11] a mean difference of 4 points was found in comfort levels measured with the DS-DAT before and after the start of palliative sedation.

Because the present study will aim to include a wider range of settings and with more variability in forms of palliative sedation, therefore the effects may be smaller. Estimating a smaller effect size of 2.4 points on the DS-DAT, using an alpha of 0.05 and 0.80 power in a two-sided, paired t-test, with a standard deviation of 6.2, and correcting for clustering due to the multiple international centre settings (using an ICC of 0.05 and pre-assumed design effect of 1.2) we will need to include 110 sedated patients. To anticipate at missing data and dropout rate during the study we aim to include 150 sedated patients in total.

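### The tests named for differences between settings assume independent patients, although the sample size section assumes clustering by centre; on the plan's own design effect a nominal 5% test rejects a true null about 8% of the time.

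*Protocol article*

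**What the plan says.** The Sample size calculation describes its allowance as "correcting for clustering due to the multiple international centre settings", "using an ICC of 0.05 and pre-assumed design effect of 1.2". That allowance is made for a paired comparison of DS-DAT scores.

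The Statistical analysis section then gives the tests for setting: "Differences between settings will be tested through a Chi-square test for categorical variables", Fisher's exact test where cells are small, and "Kruskal-Wallis test for ordinal variables, and ANOVA for continuous variables". No centre term or cluster adjustment goes with these tests. The same section announces a multilevel approach, but only for the repeated DS-DAT and RASS-PAL scores.

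The primary and secondary objectives and the Participating settings section list three kinds of setting: hospital ward, palliative care unit and hospice. The number of centres is not stated. The target is 30 sedated patients in each of five countries: "we aim to include 150 sedated patients in total".

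**The concern.** Type of unit is a property of the recruiting centre. A hospice contributes only hospice patients, so the compared factor varies between centres and not within them. If patients of one centre resemble each other, the mean for a setting rests on fewer independent pieces of information than its number of patients suggests. Chi-square, Kruskal-Wallis and ANOVA do not allow for this, so their p-values come out too small.

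The article allows for this correlation when it sets the sample size and drops it when it names the setting tests. At stake are secondary findings on how practice differs between settings. The Discussion says the study will look at such differences, and the abstract expects the results to support recommendations for practice.

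**Working it through.** **Inputs from the article.** ICC 0.05 and design effect 1.2 (Sample size calculation); three setting types (Participating settings); 150 sedated patients (Sample size calculation).

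**Assumptions.** Each centre belongs to one setting type; the three types have equal numbers of patients; the DS-DAT ICC applies to the compared variable. Centre size is not given, so it is varied.

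**Step 1: the plan's design effect.** DE = 1 + (m − 1) × ICC. Setting DE = 1.2 and ICC = 0.05 gives m = 1 + 0.2/0.05 = 5 patients per centre. The figure is consistent, and 150/5 = 30 centres, or 10 per setting type.

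The required number of 110 does not reproduce from the stated inputs. The paired formula gives (2.80 × 6.2/2.4)² ≈ 52.4, or 55 patients with the t distribution; multiplied by 1.2 these are 62.9 and 66. That is a separate matter, and nothing below uses 110.

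**Step 2: closed-form error rate.** A three-group comparison has 2 degrees of freedom and a 5% critical value of 5.99. If clustering inflates the statistic by DE, the chance of rejecting a true null is about exp(−5.99/(2 × DE)). At DE = 1.2 this is exp(−5.99/2.4) = 8.2%.

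**Step 3: simulation.** 20,000 runs per case, no true setting difference, ICC 0.05, 10 centres of 5 per setting:

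| Test | Rejection rate at nominal 5% |
|---|---|
| ANOVA | 8.0% |
| Kruskal-Wallis | 8.0% |
| Chi-square, prevalence 50% | 8.4% |
| Chi-square, prevalence 20% | 7.8% |

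The simulation standard error is about √(0.08 × 0.92/20,000) = 0.2 percentage points. With the ICC set to 0, the same code gives 4.7% to 5.1%, so the excess comes from clustering.

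**Step 4: sensitivity to what the article does not give.**

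| Case | DE | Closed form | Simulated (three tests) |
|---|---|---|---|
| ICC 0.01, m = 5 | 1.04 | 5.6% | not run |
| ICC 0.05, m = 4 (108 patients) | 1.15 | 7.4% | 6.8–7.5% |
| **ICC 0.05, m = 5** | **1.20** | **8.2%** | **7.8–8.4%** |
| ICC 0.05, unequal sizes 1 to 12, mean 5 | 1.29 | 9.9% | 9.6–9.9% |
| ICC 0.10, m = 5 | 1.40 | 11.8% | 10.9–12.0% |
| ICC 0.05, m = 10 | 1.45 | 12.7% | 11.8–12.8% |
| ICC 0.05, m = 25 | 2.20 | 25.6% | 25.8–26.4% |

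For unequal sizes, m is replaced by the size-weighted mean: Σm²/Σm = 344/50 = 6.88, so DE = 1 + 5.88 × 0.05 = 1.29. Only the bold row uses the plan's own design effect.

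**Step 5: does accounting for centre repair it?** ANOVA on centre means, which in a balanced design is equivalent to a random centre intercept, rejects in 5.2%, 5.1% and 5.3% of runs for m = 5, 10 and 25 at ICC 0.05.

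**The case against.** **Setting may mean site.** The Study population, Recruitment and Study procedures sections use the word for the individual participating site. If the tests compare sites as fixed groups, centre is the tested factor and this inflation does not arise. That reading stands as a possibility. The three types listed in the objectives and in Participating settings, and the use of setting next to country as a covariate, make unit type the likelier meaning.

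**The ICC is borrowed.** The 0.05 was assumed for the DS-DAT. The article gives no ICC for dose, length of sedation, decision-making items or satisfaction. This stands, and is why the 8% is conditional.

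**A reader might infer rates of 13%, or even 26%.** Those need centres of 10 or 25, with design effects of 1.45 or 2.2, above the plan's 1.2. They show sensitivity and are not what the article implies.

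**A reader might infer that testing settings is a stated objective.** It is not: the objectives are to evaluate comfort and sedation levels and to describe practice and evaluations. Differences between settings appear in the Discussion as something to explore, and the tests follow directly after the descriptive methods. No sample size or decision rule rests on them.

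**A reader might infer that confidence intervals will be too narrow, or that the multivariable models are wrong.** No intervals are planned for these tests. The form of the multivariable models is not stated, and a condensed article may leave that to the SAP.

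What survives is that the article itself names the unadjusted tests. This is therefore not a detail left open for the SAP.

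**Conclusion.** The point holds in a limited form. With setting read as unit type, the named tests ignore clustering that the same article assumes, and they are anti-conservative. On the plan's own design effect the error rate is about 8% instead of 5%. This rests on three assumptions: each centre has one setting type, the DS-DAT ICC carries over to the compared variables, and centres have about 5 patients each. Larger, unequal or more strongly clustered centres raise the rate, and a lower ICC brings it towards 5%.

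Only secondary comparisons are affected. It would be wrong to read this as a threat to the primary result: the change in discomfort is a within-patient comparison, and the repeated scores already have a multilevel analysis. The change is worth making, but the study's main conclusion does not depend on it.

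**What to change.** 1. State that setting means the type of unit, and use centre for the individual site.
2. Choose one of two routes for the setting comparisons. Either test them with methods that account for centre: mixed models with a random centre intercept, or GEE clustered on centre, with a small-sample correction where one is available, and a cluster-adjusted chi-square for nominal variables with several categories. Or keep the simple comparisons as description, without significance claims.
3. When the multivariable models of dose, discomfort and length of sedation are specified, include the same centre term.
4. If country is added to the setting comparison, say so, because the result is then a country-adjusted and not a crude difference.

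No new data are needed. The cost is more analysis work and larger p-values for setting differences. With few centres per setting the loss of precision is real: an analysis on centre means has 3 × (10 − 1) = 27 residual degrees of freedom with 10 centres per setting, but only 3 × (2 − 1) = 3 with two. In that case, or with sparse cells, the descriptive route may be the more practical one.

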### Dissemination

Dissemination of our findings will be presented at relevant conferences, meetings and through peer-reviewed journals, and is expected at the end of 2023. Within the EU funded project Palliative Sedation other dissemination plans are foreseen, such as an online education programme. More information about all dissemination activities can be found at the project website (www.palliativesedation.eu).

## Discussion

This study will explore the clinical practice of palliative sedation at the end of life in different palliative care settings in five European countries, and will study similarities and differences in indication, practice and specific outcomes of palliative sedation in patients with advanced cancer suffering from refractory symptoms.

### Strengths

The PALSED study is the first international multicenter study in which the palliative sedation trajectories of advanced cancer patients are observed in a standardized manner and with the main focus on the levels of discomfort in relation to the levels of sedation. Use of the same measurements in an international and multicenter context across different in-patient palliative care settings will provide valid results and may increase generalizability. Because participants can be included in the study earlier on during their palliative trajectory, in most participants the process of palliative sedation can be followed, from decision-making until the patients’ death and even afterwards by the involvement of relatives.

The use of observational measurement scales by experienced palliative care specialists, makes their evaluation more standardized and interpretable. In all settings and countries, the same questionnaires and clinical items will be observed and evaluated in a clear standardized manner. Since the main goal of palliative sedation is patient comfort, we presume that the level of symptom relief, and not unconsciousness as such, is used to guide titration of medication. Therefore, change in perceived discomfort levels could be an appropriate measurement for effectiveness, possible in combination with depth of sedation. When achievement of adequate sedation can be monitored in a patient by levels of discomfort this might result in a more tailored and proportional approach of the palliative sedation in the specific patient.

### Limitations

During preparatory meetings it became apparent that there were differences between countries and settings in the way information about palliative sedation was given. Differences in wording, timing and recipients of the given information. To stay as close as possible to daily practice, differences in the patient information sheets between the countries are respected in this study as are differences in timing of the informed consents.

Patients with rapid deterioration where the decision to start palliative sedation is very sudden may be missed for inclusion, since the time for informed consent procedures is limited and they need to give informed consent themselves. When these patients are included, missing data can be expected for measurements when the clinical situation requires a rapid response and time for study measurements are limited.

The absence of a validated scale for measuring comfort in patients with palliative sedation is a limitation, but discomfort in non-communicative patients at the end of life has been studied before. In patients receiving continuous palliative sedation, van Deijck and colleagues used discomfort as the primary outcome [11] which was also measured with the DS-DAT [15]. They concluded that the face validity of the DS-DAT for monitoring discomfort in palliative sedated patients appears to be good, as the items of the scale correspond to the current clinical assessment and the recommendations of some guidelines of measuring discomfort by facial expressions and body movements. Soto-Rubio et al. studied the initial psychometric properties of a discomfort observation scale, containing the same items as the DS-DAT, in a cohort of patients with palliative sedation and concluded that it had an adequate model fit [12].

In an earlier version of the protocol, we had envisioned that independent observers would complete the measurements of discomfort levels [20]. However, due to the start of the study recruitment during the COVID-19 pandemic, we were faced with limited access to the in-patient settings and participants. Therefore, we decided to train health care professionals working at the bedside in the measurements of DS-DAT and RASS-PAL. This can be seen as a limitation of the study because there is no longer an independent measurement. On the other hand, using the observations of experienced caregivers and collecting them in a uniform way can also be a strength which might support the daily clinical practice of monitoring simultaneously.

## Data Availability

The datasets generated during and analysed during the current study will be made publicly available. To permit the widest re-use of data as possible, the non-sensitive data will be made available as open access in DANS EASY. Before submitting the data in DANS, the Radboud University will check the data quality.

## Abbreviations

DS-DAT: Discomfort Scale--Dementia of Alzheimer Type
RASS-PAL: Richmond Agitation Distress Scale-modified version for Palliative care
ESAS: Edmonton Symptom Assessment System
ECOG PS: Eastern Cooperative Oncology Group Performance Status
